### Sample size calculation

To determine the required sample size for measuring differences in quality of life between the two conditions (group training and waiting list), the sample size is calculated by power analysis. The effect size of cognitive behavioral therapy for quality of life is not well known, because in other effect studies the outcome is usually measured in terms of physical symptoms. Therefore, we have to use effect size of cognitive behavioral therapy for physical symptoms as an available estimator for the (shortage of) quality of life. The effect size of cognitive behavioral therapy for physical symptoms ranges from .00 to .95 [8], suggesting a medium effect for cognitive behavioral therapy for physical symptoms. Assuming this effect also applies for quality of life, the magnitude of the effect size following Cohen's (1988) [28] is 0.50. With a power of .80 and an alpha of .05 (two-tailed), a sample size of 100 patients (50 in each condition) is required.

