**Methods and design:**

A randomized controlled trial is designed. One hundred patients are randomized to either the group training or the waiting list.

Physicians in general practices and outpatients clinics of general hospitals refer patients. Referral leads to inclusion if patients are between 18 and 65 years old, understand Dutch, have no handicaps impeding participation and the principal DSM-IV-TR classification is undifferentiated somatoform disorder or chronic pain disorder. In contrast to other treatment effect studies, the co-morbidity of a personality disorder does not lead to exclusion. By this, we optimize the comparability between the study population and patients in daily practice enlarging the generalization possibilities.

Also in contrast to other effect studies, we chose quality of life (SF-36) instead of physical symptoms as the primary outcome measure. The SF-6D is used to estimate Quality Adjusted Life Years (QALYs). Costs are measured with the Trimbos/iMTA Questionnaire for Costs associated with Psychiatric Illness. Measurements are scheduled at baseline, after the training or waiting list, three and twelve months after the training. The differences between measurements are analyzed according to the intention-to-treat principle. The cost-effectiveness is expressed as costs per QALY, using multiple sensitivity analyses on the basis of a probabilistic model of the trial.

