**Figure 1 F1:**
[figure not shown]
**Design of the randomized controlled trial**.

The study started February 2005. The inclusion of patients has ended in September 2008. The one-year follow-up period of the randomized patients will be finished in April 2010.

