Patients are recruited from general practices and outpatient clinics of general hospitals in and nearby Rotterdam, the Netherlands. Physicians' attention is drawn to the group training by periodical postcards informing them when and how they can refer patients to the group training. Patients' attention is drawn to the group training by announcements in local newspapers and on websites of patients' associations, in which they are asked to make an appointment with their physician to discuss referral when interested. Physicians decide whether the physical symptoms are medically explained or unexplained hereby checking the first exclusion criterion, after which they refer patients when they find this appropriate. After referral, patients are invited for an interview, preferably in a medical setting, in which they are verbally and in writing informed about the study. In this interview, the first three inclusion criteria and the last exclusion criterion are verified. After receiving patients' signed informed consent, patients are invited for a second interview, in which the last inclusion criterion and the second exclusion criterion are investigated by the Structured Clinical Interview for DSM-IV Axis I Disorders/Patient edition (SCID-I/P) administered by independent psychologists. These psychologists make the final decision based on the results of the SCID-I/P whether patients' UPS can be classified as an undifferentiated somatoform disorder or as a chronic pain disorder and whether this disorder is the principal DSM-IV-TR classification. If undifferentiated somatoform disorder or chronic pain disorder is the principal DSM-IV-TR classification, then patients complete the self-report questionnaire for DSM-IV Axis II personality disorders (VKP).

Right before the start of each next training, the newly included patients fill in the questionnaires. Subsequently, an independent statistician randomizes them to either the group training or waiting list with a computer-based 1:1 ratio randomization procedure. The results of this randomization procedure are sent to the patient by letter. If randomization leads to starting with the group training, then an invitation for the group training is enclosed in the randomization letter. After the group training or after a waiting-period of the same length as the group training, all patients fill in the questionnaires for the second time.

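### Fifty patients per condition gives about 70% power, not 80%, for an effect size of 0.50 at two-tailed alpha .05; the stated inputs require 64 per condition

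*Protocol article*

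**What the plan says.** The Sample size calculation section of the protocol article sets out to size the comparison of quality of life between group training and waiting list. It reports that earlier effect sizes for physical symptoms range from .00 to .95, takes this as a medium effect, and assumes 0.50 for quality of life. It then states: "With a power of .80 and an alpha of .05 (two-tailed), a sample size of 100 patients (50 in each condition) is required".

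The abstract repeats the total: "One hundred patients are randomized to either the group training or the waiting list". The Study population section describes a "computer-based 1:1 ratio randomization procedure", so the conditions are meant to be equal in size. The text below Figure 1 adds: "The inclusion of patients has ended in September 2008".

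The sample size section names no test. It mentions no correlation between baseline and outcome, no gain from repeated measurement and no loss to follow-up. The clinical evaluation part of the statistical analyses plans a mixed model with the baseline value as covariate, but the sample size section does not refer to it.

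**The concern.** The section gives everything that a standard two-group calculation needs: effect size, alpha, number of tails, power and two equal groups. A medium effect of 0.50 at two-tailed .05 and 80% power is a familiar benchmark, and its answer is in the low sixties per group, not 50. The gap is too large to be rounding.

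This is the trial's only justification of its size, and the discrepancy runs in the favourable direction. On the calculation as written, a true effect of the planned size would be missed about 3 times in 10 instead of 2 in 10. A reader who relies on the stated 80% would give a null result more weight than the design supports.

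**Working it through.** **Inputs, all from the protocol article**

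- Standardised effect d = 0.50, so SD = 1 (Sample size calculation)
- Alpha .05, two-tailed; power .80 (same section)
- Two independent conditions, 1:1 (Sample size calculation; Study population)
- Stated result: 50 per condition, 100 in total

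**Step 1. Attempt to reproduce the stated figure.** Normal approximation for two means:

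n per arm = 2(z₁₋α/₂ + z₁₋β)² / d² = 2(1.960 + 0.842)² / 0.25 = 62.8, so 63.

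The t-test (noncentral t) gives 63.77, so 64 per arm and 128 in total. The stated 50 is not reproduced. It is 14 per arm (28 patients) short of the t-test answer.

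**Step 2. Power at 50 per arm.** The noncentrality is d√(n/2) = 0.50 × √25 = 2.50, on 98 degrees of freedom.

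- Two-tailed .05, t-test: power 0.697 (normal approximation 0.705).
- Effect detectable with 80% power: d = 0.566 (normal approximation 0.560).

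**Step 3. Which inputs do give 50?**

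- One-tailed .05, power .80: 2(1.645 + 0.842)² / 0.25 = 49.5, so 50. The t-test gives 50.15, and power at 50 is 0.799.
- Two-tailed .10 with power .80: 50 (normal approximation).
- Two-tailed .05 with power .70: 50 (normal approximation).

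One tail at .05 is the route that keeps the stated alpha and power and changes only the sidedness.

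**Step 4. Credit for the planned baseline adjustment.** With baseline as covariate, the residual variance is multiplied by 1 − r², where r is the correlation between baseline and the 13-week value. The effective effect is 0.50/√(1 − r²). The article gives no r, so the values below are assumptions. Power is two-tailed by t-test, with 50 evaluable per arm:

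| r | effective d | power |
|---|---|---|
| 0 | 0.500 | 0.697 |
| 0.3 | 0.524 | 0.737 |
| 0.4 | 0.546 | 0.771 |
| 0.47 | 0.566 | 0.801 |
| 0.5 | 0.577 | 0.816 |
| 0.6 | 0.625 | 0.872 |

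Eighty percent is reached at r = 0.468 (about 0.45 by the normal approximation).

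**Step 5. Sensitivity to loss.** The article gives no loss rate, so 10% and 20% are illustrations.

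| Evaluable per arm | Unadjusted power | Power at r = 0.5 | r needed for 80% |
|---|---|---|---|
| 50 (no loss) | 0.697 | 0.816 | 0.47 |
| 45 (10% loss) | 0.650 | 0.773 | 0.55 |
| 40 (20% loss) | 0.598 | 0.722 | 0.62 |

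**The case against.** The strongest reply is that 70% is not the power of the analysis that will be run. The clinical evaluation uses a mixed model with the baseline value as covariate, and the sample size section names no test. If 0.50 is expressed in raw SD units, adjustment with a moderate correlation takes 50 evaluable patients per arm to 80% or beyond. This stands to the extent that true power is unknown and may lie above or below 80%. It does not rescue the statement: the section presents 50 per condition as following from effect size, alpha and power alone, and nothing in the article supports a correlation of about 0.47 with no losses. The later measurements cannot supply the missing power for the between-group contrast either, because waiting-list patients are offered the training after the second measurement and the Discussion acknowledges that follow-up has no control condition.

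Second, the one-tailed explanation is an inference. Other routes lead to 50, and by the exact t-test the one-tailed figure is 50.15, which strictly rounds up to 51. That is fair. The match is a likely cause, not a documented one, and the mismatch stands whatever its origin.

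Third, a condensed article may leave a dropout allowance to the full protocol. Agreed: the loss figures above show only how little margin there is, and the conclusion does not depend on them.

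Finally, inclusion has ended and the correction changes no endpoint or analysis. This limits the remedy to a restatement. It does not make the stated power right.

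**Conclusion.** The concern holds. On the article's own inputs, 80% power at two-tailed .05 for an effect of 0.50 needs 64 patients per condition (128 in total), against the stated 50 (100 in total). Fifty per condition gives 69.7% power, about 10 percentage points short, or 80% power for an effect of 0.57. These figures assume an unadjusted two-sample comparison with all 100 patients evaluable. The planned baseline-adjusted model may have higher power, but 80% then rests on an unstated correlation of at least about 0.47 without loss, and more with loss. The arithmetic is certain; the use of one tail is the probable explanation only.

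**What to change.** Replace the concluding sentence of the Sample size calculation section with a statement such as: *With 50 evaluable patients per condition, an unadjusted two-sample comparison at two-tailed alpha .05 has 70% power for an effect size of 0.50, or 80% power for 0.57; 64 per condition would be needed for 80% power at 0.50.*

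If the sponsor prefers to credit the baseline-adjusted model, the section should state the assumed correlation between baseline and outcome, its source, and the assumed loss to follow-up, next to the resulting power. The correlation must be at least about 0.47 with no loss, about 0.55 with 45 evaluable per condition and about 0.62 with 40. It should be justified from data or literature, not solved backwards from 100 patients.

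The cost is one corrected sentence and a less favourable power figure. No further patients are needed, and the endpoints and analysis stay as they are.

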### Statistical analyses

The comparability of the patients' baseline-variables between the two conditions (group training and waiting list) is analyzed with the two-tailed t-tests for independent samples for the continuous variables, with the two-tailed Mann-Whitney U-tests for the ordinal variables and with the chi-square tests for the categorical variables. If the patients in the two conditions are not comparable on one or more baseline-variables, those variables will be utilized as covariables in the subsequent analyses.

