### Statistical analyses: clinical evaluation

The clinical evaluation is conducted according to the intention-to-treat principle. The effectiveness of the group training for primary and secondary outcome measures is analyzed with mixed modeling (i.c. random regression modeling). Baseline measurements, corresponding to the subsequent outcome measurements, are entered as covariables. This method of mixed modeling for repeated measurements enables the use of flexible error covariance structures. In addition, the predictive performance of baseline-variables, especially personality variables, on effectiveness can be estimated.

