## Discussion

The primary aim of our study is to investigate (cost-)effectiveness of an easily accessible protocollized group training for patients with UPS in primary care in the daily practice of our mental healthcare institution, Riagg Rijnmond, The Netherlands.

Investigating the (cost-)effectiveness of our training in the daily practice of a mental healthcare institution has its benefits and its limitations. The huge advantage of investigating the (cost-)effectiveness in the daily practice is that if (cost-)effectiveness is shown, the group training can be started without the delay of practical implementation issues. The limitations for this study are less possibilities for exclusion of patients and for the control condition.

Consequently, the (cost-)effectiveness is explored in a heterogeneous group of patients. Measuring heterogeneity of our study population with the SCID-I/P and VKP but not excluding co-morbidity and drawing attention to the group training by announcements to both physicians and patients acumilate this heterogeneity. Patients being referred on their own initiative are probably more motivated than patients being referred on their physician's initiative. On the one hand, this enhances the probability of a representative study population, whose heterogeneity will be equally divided between the two conditions by randomization. Furthermore, this heterogeneous study population is real practice, making the study results realistic estimates of that practice. On the other hand, the group training might be effective by only treating the co-morbidity, like anxiety. Analyzing the predictability of this co-morbidity and other baseline variables on (cost-)effectiveness can solve this limitation.

Because the daily practice only allows a waiting list for a short period, the follow-up measurements do not have a control condition. Repeated measurements in the same patients and using a probabilistic model can solve this problem partly.

If we show that our group training is feasible in daily practice and (cost-)effective, more patients with UPS could be served, their quality of life could be improved while costs might be decreased.

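### Significance tests of baseline differences choose the extra covariates, so the outcome models depend on chance imbalance and lose some precision

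*Protocol article*

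**What the plan says.** In the protocol article, Statistical analyses, baseline comparability of the two arms "is analyzed with the two-tailed t-tests for independent samples for the continuous variables, with the two-tailed Mann-Whitney U-tests for the ordinal variables", with chi-square tests for categorical variables. The next sentence turns the result into a modelling rule: "If the patients in the two conditions are not comparable on one or more baseline-variables, those variables will be utilized as covariables". It applies to the analyses that follow, so it reaches the SF-36 summary scores, which are the primary outcome. No significance level, number of variables or other criterion is given, so the tests are the only stated meaning of comparability.

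Statistical analyses: clinical evaluation adds one covariate that does not depend on any test: "Baseline measurements, corresponding to the subsequent outcome measurements, are entered as covariables". Allocation, under Study population, is by a "computer-based 1:1 ratio randomization procedure" run by an independent statistician. Sample size calculation gives the planned size: "a sample size of 100 patients (50 in each condition) is required".

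**The concern.** When allocation is random, the hypothesis that the arms come from the same population is true by design. A significant baseline test then marks a chance difference. Whether a variable deserves adjustment depends on how strongly it predicts outcome, and the test carries no information on that.

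The rule can go wrong in two ways. It can bring in variables that are unbalanced by chance but unrelated to outcome. It can also leave out variables that predict outcome because their imbalance falls short of significance in a trial of 100. The article itself expects personality disorder and co-morbidity to influence the effect of the training, yet this rule adjusts for them only if a test happens to be significant. At stake are the precision of the primary comparison and a primary model that can be written down before the data are examined.

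**Working it through.** **Inputs.** From the article: 50 per arm, effect size 0.50, two-tailed alpha 0.05, baseline outcome score always in the model. Assumed: baseline tests at 0.05 (no level is stated), and the correlations given below.

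**The planned size.** A two-tailed calculation gives 2 × (1.96 + 0.84)² / 0.50² = 62.7, so 63 per arm. A one-sided 0.05 test gives 50. The stated 50 per arm therefore does not follow from its two-tailed inputs, and it gives about 70% power for an unadjusted comparison. That is a separate matter, but it makes precision from covariates more valuable. The steps below use 50 per arm as planned.

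**Selection by chance.** For k independent tests the chance of at least one significant result is 1 − 0.95^k:

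| k | chance of at least one |
|---|---|
| 5 | 23% |
| 10 | 40% |
| 20 | 64% |
| 30 | 79% |

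The expected number is 0.05 × k, so one for k = 20. The SF-36 (8 scales, 2 summaries) and SCL-90-R (8 scales, 1 index) already make 19 variables. They are correlated, so for about 20 variables 64% is a ceiling.

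**Imbalance passed over.** The standard error of a standardised difference is √(2/50) = 0.20. The critical t on 98 df is 1.984, so significance needs 1.984 × 0.20 = 0.40 SD. An imbalance of 0.30 SD gives t = 0.30 / 0.20 = 1.5, p = 0.14.

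**What such an imbalance does.** With a slope of 0.2 to 0.3 outcome SDs per covariate SD, 0.30 SD shifts the estimate by 0.06 to 0.09 SD, which is 12% to 18% of 0.50. If 0.2 to 0.3 are instead partial correlations given a baseline score correlated 0.5 with outcome, multiply by √(1 − 0.5²) = 0.87, giving 0.05 to 0.08 SD. For any one covariate, an imbalance of at least 0.30 SD arises in about 13% of trials. The mean absolute imbalance is 0.20 × √(2/π) = 0.16 SD, a shift of about 0.03 to 0.05 SD before the 0.87 factor.

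**Power and error rate.** Simulation with 50 per arm, baseline score always adjusted (assumed correlation 0.5 with outcome), 20 independent candidates tested at 0.05, and one or three of them prognostic with partial correlation about 0.25:

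| prognostic covariates | type I error, test-selected | power, test-selected | power, fixed in advance |
|---|---|---|---|
| 1 | 4.7% | 79% | 83% |
| 3 | 4.5% | 80% | 87% |

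The mean estimate under the rule was 0.50 for a true 0.50. Repeating this with partial correlations from 0.2 to 0.3 (10,000 runs per setting) gave a power gap of about 3 to 5 points with one covariate and about 5 to 10 with three. In those runs the rule also had 1 to 2 points less power than adjusting for the baseline score alone.

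**The case against.** The best defence is that the clinical evaluation always adjusts for the baseline score of the outcome, usually the strongest predictor. This stands, and it is the main reason the harm is modest. A simulation with one covariate and no baseline score shows much larger gaps, such as 71% against 82% power at a correlation of 0.5 and 72% against 93% at 0.7. Those figures credit the missing covariate with what the baseline score already supplies, so they should not be used here.

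A reader might infer that data-driven selection inflates false positives or biases the estimate. Neither is supported. The simulated type I error is at or slightly below 5%, and the estimate is centred on the true value. The shift from an unadjusted imbalance is a chance shift in a particular trial, not a bias of the procedure.

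A reader might also take the 19 scales as 19 independent chances of selection. They overlap, the summaries repeat the scales, and each outcome's own baseline is already in its model.

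A condensed article may leave a covariate list to a fuller document, so the absence of a list is not the fault. The fault is the selection rule that is stated. Nor does the Discussion's remark on a heterogeneous population "whose heterogeneity will be equally divided between the two conditions by randomization" bear on this: it contains no covariate rule.

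**Conclusion.** The point holds in limited form. The stated rule selects covariates by chance imbalance, makes the primary model depend on the data, and passes over prognostic variables whose imbalance is below about 0.40 SD at 50 per arm. The cost is a modest loss of precision and a slightly conservative test. At assumed partial correlations of about 0.25 the power loss is about 4 percentage points with one prognostic covariate (83 − 79) and 7 with three (87 − 80). These sizes rest on assumptions the article does not settle: a test level of 0.05, 20 independent candidates, and a baseline-outcome correlation of 0.5. That the rule exists and is poorly chosen is certain; its size in this trial is not. It should be changed, but it does not threaten the validity of the primary comparison.

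**What to change.** Delete the sentence that makes covariates depend on baseline tests, and describe the arms at baseline without p values. Before outcome data are seen, fix a short covariate set and use it whatever the imbalance: the baseline score of the outcome (already planned) plus a few prognostic variables that the article shows are available, such as age, DSM classification from the SCID-I/P and VKP personality disorder. Label any other adjustment a sensitivity analysis. The article reports that inclusion ended in September 2008, so whoever chooses the list should not have had access to outcome data, and this should be recorded.

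Referral source should not be on the list unless it was recorded; the article discusses it but does not say that it was. If randomisation batch is included, use a random effect. With 13-week trainings run back to back from February 2005 to September 2008 (assumed; about 187 weeks, 187 / 13 = 14.4), there could be about 14 batches of roughly 7 patients, and fixed effects would take 13 degrees of freedom.

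The change replaces one paragraph, needs no new data for the variables named, and costs a few degrees of freedom.
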